### Adverse events

The qualified investigator will follow adverse events with start dates occurring any time after informed consent is obtained until 7 days (for non-serious adverse events) or 30 days (for severe adverse events) after the last day of study participation. At each study visit, the investigator (or designee) will inquire about the occurrence of adverse events (AE)/serious adverse events (SAEs) since the last visit and record in participant research record and case report form. Events will be followed for outcome information until resolution or stabilization. This trial is a low risk, non-invasive intervention, with minimal adverse events anticipated and hence anticipation of low rate of loss to follow-up. Nevertheless, hypertension is a chronic disease, and it is possible that the complete 1 year follow-up will not occur for all patients and has a built in 20% loss in the sample size estimation.

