### Outcomes

The primary outcome will be a successful increase in potassium intake to > 90 mmol/day as estimated from the 24-h urinary sample at 4 weeks. The secondary outcomes are persistence of increase in potassium intake (to > 90 mmol/day) at 1 year. For examination of safety, the following outcomes will be specifically examined: hyperkalemia (as defined as a serum potassium > 5.1 mmol/L) at 4 weeks after initiation of dietary counselling, at 1 and 4 weeks after starting potassium supplements, 1 week after dose escalation/dispensing, and at 12 months in everyone and gastrointestinal side effects (change in bowel habits, belching and/or flatulence; abdominal pain or cramps). Additional patient-reported adverse effects will also be measured and reported. Serious adverse events will be captured and reported as per regulatory requirements.

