### Sample size and analytical plan

The study goal is to estimate the success rate of the dietary intervention, as well as the success rate of the two-stage approach. Dietary counselling alone will not exceed this degree of increase which was seen with supervised intake and meal provision, but there are no robust data to support an estimate of its effect. However, potassium supplementation at the dose proposed would very likely result in achieved potassium intake of > 90 mmol/day in all participants. A sample size of 100 participants will allow us to able to estimate both success rates to within a margin of error of at most 5%. At 4 weeks, there should be little loss to follow-up; however, we estimate this to be about 20% to be conservative. Thus, this trial will enrol 120 participants. Furthermore, there are no plans for additional analyses including subgroup. Multiple imputation will be done for any missing data.

The primary outcome is a simple proportion of the participants who are able to achieve an increase in potassium intake. Secondary outcomes of the proportion of participants with persistent adequate potassium intake at 52 weeks, and safety outcomes, will also be reported as proportions. For the secondary outcomes of change in sodium, potassium, and blood pressure, the mean differences will be calculated and reported, and a paired *t*-test will be used to compare for statistical significance. There will be no interim analysis.

The proportions will be summarized as absolute numbers and percentages. Continuous outcomes will be reported as mean (and 95% confidence intervals). A *p* value of < 0.05 will be used for the paired comparisons of the continuous outcomes (i.e. secondary outcomes of change in sodium, potassium and blood pressure).

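### Enrolling 120 with 20% loss leaves 96 evaluable participants, not 100, and the single 20% allowance is tied to week 4 in one section and to 1 year in another

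*Protocol article*

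**What the plan says.** All statements are in the Methods of the protocol article.

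- **Sample size and analytical plan, target:** "A sample size of 100 participants will allow us to able to estimate both success rates to within a margin of error of at most"; the limit given is 5%. The two rates are those of the dietary intervention and of the two-stage approach.
- **Same section, loss:** "At 4 weeks, there should be little loss to follow-up; however, we estimate this to be about 20% to be conservative".
- **Same section, enrolment:** "Thus, this trial will enrol 120 participants".
- **Same section, missing data:** "Multiple imputation will be done for any missing data".
- **Adverse events:** low loss is expected, but "it is possible that the complete 1 year follow-up will not occur for all patients", and the trial "has a built in 20% loss in the sample size estimation".
- **Outcomes:** the primary outcome is success "as estimated from the 24-h urinary sample at 4 weeks". A secondary outcome is "persistence of increase in potassium intake (to > 90 mmol/day) at 1 year".

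**The concern.** The enrolment figure is presented as following from the target of 100 and the loss of about 20%. It does not: at that loss, 120 enrolled do not yield 100 evaluable. The number on which the primary precision statement rests is therefore slightly too high.

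Separately, the sample size contains only one allowance, the step from 100 to 120. One section places it at the 4-week primary time point, and the other offers it as cover for incomplete follow-up at 1 year. Loss accumulates, so the choice affects what a reader should expect. If 20% is the loss at week 4, then 96 is the week-4 number and the 52-week number can only be the same or lower. If 20% is the cumulative loss to 52 weeks, then 96 is the 52-week number and the week-4 number is the same or higher. The article does not say which is meant.

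**Working it through.** **Inputs.** Target evaluable number 100, loss about 20%, enrolment 120 (all from Sample size and analytical plan). Time points are 4 weeks for the primary outcome and 1 year for persistence (Outcomes).

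**1. Reproduce the plan's figure.**
- Multiplying the target by (1 + loss): 100 x 1.20 = 120. This matches the stated enrolment exactly.
- Dividing the target by (1 - loss): 100 / 0.80 = 125. This does not match.

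So 120 was reached by adding 20% of the target, whereas loss is a fraction of those enrolled.

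**2. What 120 delivers.**
- Evaluable at 20% loss: 120 x (1 - 0.20) = 96, which is 4 short of 100.
- Largest loss that still leaves 100: (120 - 100) / 120 = 16.7%.

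**3. Effect on precision.** The 95% half-width for a proportion is 1.96 x sqrt(p(1 - p)/n).

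| True success rate | n = 100 | n = 96 |
|---|---|---|
| 0.5 (worst case) | 1.96 x sqrt(0.25/100) = 9.8 points | 1.96 x sqrt(0.25/96) = 10.0 points |
| 0.9 | 1.96 x sqrt(0.09/100) = 5.9 points | 1.96 x sqrt(0.09/96) = 6.0 points |

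The shortfall costs about 0.2 points at worst.

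**4. The time point.** The two possible meanings of the one allowance, for 120 enrolled:

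| Meaning of 20% | Evaluable at week 4 | Evaluable at week 52 |
|---|---|---|
| Loss at week 4 (sample size section) | 96 | at most 96 |
| Cumulative loss to 1 year (Adverse events section) | between 96 and 120 | 96 |

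Under the second meaning the worst-case half-width at week 4 lies between 10.0 points (n = 96) and 1.96 x sqrt(0.25/120) = 8.9 points (n = 120). The primary outcome is then no worse off than under the first meaning, and the 52-week outcome has a defined allowance. Under the first meaning the article makes no provision for loss between week 4 and week 52.

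**The case against.** The case for leaving the text alone has several parts.

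- **The 20% is a cushion, not a forecast.** The sample size section expects little loss at 4 weeks and calls 20% conservative, and the Adverse events section also expects low loss. If week-4 loss is in fact small, most of the cushion remains for 52 weeks. This stands. A reader might infer that the two sections are strictly incompatible unless nobody is lost after week 4, but that would hold only if 20% were a prediction for week 4. What remains is that the text never states the cushion reading.
- **The loss is only about 20%, and 120 tolerates 16.7%.** This softens the arithmetic but does not remove the error, since the Adverse events section restates the allowance as a plain 20%.
- **Multiple imputation is planned.** The analysis is therefore not simply one of completers. That is correct, but imputation adds no observed participants and does not turn 96 into 100.
- **Nothing turns on four participants.** The primary outcome is a descriptive proportion with no test or power requirement, and the half-width changes by about 0.2 points. This stands and sets the severity.
- **An article may leave detail to the full protocol.** That answers an omission. Here the article prints both the derivation and the two time points, so the correction belongs in the article.

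**Conclusion.** The point holds, with minor severity. As written, the derivation of 120 is wrong: at 20% loss it leaves 96 evaluable, and 100 would need 125 enrolled or a loss of no more than 16.7%. The one allowance is attached to two time points without saying which it protects. The supported effect is a worst-case 95% half-width of about 10.0 points instead of 9.8, assuming a simple normal-approximation interval and exactly 20% loss.

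Two stronger conclusions should not be drawn.

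- A reader might infer that the precision of the 52-week outcome is overstated. The protocol states no precision for that outcome; its margin of error refers to the dietary and two-stage success rates.
- A reader might also compound a second 20% loss after week 4, giving 120 x 0.8 x 0.8, or about 77 participants. The documents give no such second loss, and the Adverse events section anticipates a low rate.

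The stated 5% margin is a separate matter. Even 100 participants give 9.8 points in the worst case, so correcting 100 to 96 does not by itself repair that statement, and the gap from 5% should not be counted towards the weight of this point.

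**What to change.** Keep enrolment at 120 and reword two places.

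1. **Sample size and analytical plan:** state that 120 enrolled with 20% loss gives an expected 96 evaluable participants, or that 120 retains 100 if loss does not exceed 16.7%. Base the primary precision statement on the number chosen; for 96 the worst-case 95% half-width is about 10.0 points.
2. **Sample size and analytical plan, and Adverse events:** name the same time point for the 20% in both. If it is meant as the cumulative loss to 52 weeks, with less expected by week 4, one sentence saying so resolves the inconsistency.

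The cost is a few sentences and slightly less favourable stated figures. No extra participants are needed, and neither trial conduct nor the primary outcome changes.

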### Data safety monitoring board

This study will be monitored by an independent data safety monitoring board (DSMB), consisting of a clinical epidemiologist, a nephrologist, and a biostatistician. The DSMB will be immediately informed of any SAEs which may potentially be related to the study intervention. Other SAEs will be reviewed during regular DSMB meetings. Interim reports, prepared by the data management team for the study, for review by the DSMB will include data on recruitment, compliance, adverse effects, baseline comparability, and treatment comparisons. An agreed upon review package which contains the appropriate data summary by treatment will be provided by the study statistician for the purposes of these reviews.

### Study management

A trial management team involving principal investigators (SH and MR), three co-investigators (DF, GK, TR), and one of study coordinator and research assistant will review, implement, and supervise all aspect of this study. The responsibility for study design, data collection, interpretation, and writing of the manuscript and decision to submit the report for publication reside with the research team and not the funding sponsor. The Project Management Group will meet every 6 months to review trial conduct.

Access to medical records and study data will be limited to authorized personnel listed on the study delegation log or permitted by the study agreement. All data collected during the course of research will be kept strictly confidential and accessed by members of the study team. Access to electronic data will be password protected and auditable, electronic data will be stored on a hospital network with firewall and security back-up measure in place, and paper copies of the study data will be stored securely in locked cabinets and in locked offices.

Participants will be allocated an individual trial identification number and will be store in a secure database. Only the research team will have access and control over the trial dataset. The final trial data for this protocol can be available upon request. The datasets analysed during the current study and statistical code are available from the corresponding author on reasonable requests, as is the full protocol. In addition, there is no anticipated harm and compensation for trial participation. All participants will continue to receive standard of care post trial.

## Discussion

There is unequivocal evidence on the efficacy of potassium intake in lowering blood pressure and subsequent cardiovascular outcomes. However, the trials have not resulted in change in practice due to a lack of data on the most effective methods to implement this change. Our adaptive trial design, with sequential intervention of the dietary counselling, followed by additional supplementation in those in whom diet alone is ineffective, represents an easy to implement intervention. This might bridge the efficacy to effectiveness implementation gap. A 5-mm Hg decrease in systolic blood pressure, as reported with additional potassium effect in meta-analyses, translates into one less antihypertensive medication. Thus, the results of this trial have the potential for a very large scale impact at a public health, as well at an individual level. Lifestyle habits to improve blood pressure and decrease medication burden have been already identified as high level research priorities by patients in work done by Hypertension Canada and others. We hope the results of this trial, once completed and reported, will provide useful and actionable information for public health in this sphere.

## Trial status

The trial has received ethics approval from the Ottawa Health Science Research Ethics Board (OHSN-REB) on February 5, 2019, reference number 20180873-01H. Trial screening and recruitment has begun in January 2020, with anticipated completion in 2023. Protocol version and date: January 21, 2022. The datasets analysed during the current study and statistical code are available from the corresponding author on reasonable request, as is the full protocol.

## Data Availability

Supplementary material including a simple 3 question survey.

## Abbreviations

BP: Blood pressure
ABPM: Ambulatory blood pressure monitoring
DSMB: Data safety monitoring board
GFR: Glomerular filtration rate
SBP: Systolic blood pressure
DBP: Diastolic blood pressure
TOH: The Ottawa Hospital
AE: Adverse events
SAE: Severe adverse events
